## **7. Randomization and allocation concealment**

### Sequence generation

Randomization sequence will be generated via computerized random number generator in blocks of 5-10 participants in CBT-I and SET(1:1).

### Allocation concealment

Allocation concealment will be maintained using sequentially numbered, opaque, and sealed envelopes.

## **8. Blinding**

Participants will be partially blinded, as the study will be advertised as a research study to evaluate whether one or another insomnia treatment will improve insomnia. The program content will not be revealed. Participants will blind to study hypotheses and content of other treatment group through study duration.

Investigators and outcome assessors will be blind to allocation.

## **9. Safety Monitoring Plan**

Safety monitoring will be conducted throughout the study; therefore, safety concerns will be identified by continuous review of the data by the PI, internal quality assurance checks, and DSMB.

Participants will be given a 24-hour telephone number for calling the physician to feelings of depression or suicide thoughts. In the event that significant medical or psychiatric problems are encountered, the study blind will be broken so that appropriate medical treatment will be provided.

The PI will designate appropriately qualified personnel to periodically perform quality assurance checks during and after the study. Such monitoring will provide the opportunity to

evaluate the progress of the study and to obtain information about potential problems. The monitor will assure that data are accurate and in agreement with any paper source documentation used, verify that subjects' consent for study participation has been properly obtained and documented, confirm that research subjects entered into the study meet inclusion and exclusion criteria, verify that study procedures are being conducted according to the protocol guidelines, monitor review AEs and SAEs, and assure that all essential documentation required by Good Clinical Practices (GCP) guidelines are appropriately filed. At the end of the study, they will confirm that the site has the appropriate essential documents on file, and advise on storage of study records.

An independent Data and Safety Monitoring Board will meet during the enrollment and follow-up and at trial end to review safety data. The Board will be blinded to subjects' actual randomized group assignments but may request at any time that the blind be broken, if concerns arise from the blinded data. Ad hoc meetings will be convened if SAEs occur that are considered at least possibly related to the study procedures.

## **10. Ethics**

### IRB Review

The study is conducted under a protocol reviewed by the UCLA IRB; the study is conducted by scientifically and medically qualified persons; the benefits of the study are in proportion to the risks; the rights and welfare of the subjects are respected; the physicians conducting the study ensure that the hazards do not outweigh the potential benefits; the results reported will be accurate; subjects give their informed consent and are competent to do so and not under duress; and all study staff comply with the ethical principles in 21 Code of Federal Regulations (CFR) Part 50 and the Belmont Principles.

### Protocol Modifications

All necessary protocol changes are submitted in writing as protocol amendments to the IRB by the PI for approval prior to implementation. The only protocol modification was extension of the follow-up period from two to three years. See above note regarding use of DSM-5 criteria following update to DSM-IV after start of this trial.

#### Ethical Conduct of the Study

This study is conducted in accordance with all applicable Federal human research protections requirements and the Belmont Principles of respect for persons, beneficence, and justice. The procedures set out in this study are designed to ensure that all study personnel abide by the principles of the ICH GCP Guideline and the Code of Federal Regulations (CFR). The PI confirms this by signing FDA Form 1572.

#### Confidentiality of Data and Subject Records

To maintain subject confidentiality, all laboratory specimens, eCRFs, reports and other records are identified by a subject number only. Research and clinical records are stored in a locked cabinet. Only research staff, and other required regulatory representatives have access to the records. Subject information are not released without written permission.

#### Compensation for Participation

Subjects are compensated for travel expenses and for time contributed to this research study in the form of cash. Compensation is provided at each subject visit and is detailed in the informed consent form.

#### Written Informed Consent

The informed consent process and document is reviewed and approved by the IRB and prior to initiation of the study. The consent document contains a full explanation of the possible risks, advantages, and alternate treatment options, and availability of treatment in the case of injury, in accordance with 21 CFR Part 50. The consent document indicates that by signature, the subject. A written informed consent document, in compliance with 21 CFR Part 50, 32 CFR Part 219, and the Belmont Principles, and HIPAA Authorization is signed by the subject before

any study-related procedures are initiated for each subject. All potential subjects for the study are given a current copy of the Informed Consent Form to read. All aspects of the study and informed consent are explained in lay language to the subject by either the investigator, or a medically trained designee. Any subject who is unable to demonstrate understanding of the information contained in the informed consent will be excluded from study participation. All study subjects are given a copy of the signed informed consent.

## **11. Data Handling and Record Keeping**

Source documents include but are not limited to original documents, data and records such as interview data, questionnaire data, and laboratory results. Data will be transcribed from source documentation directly into a statistical program (i.e., SPSS). Paper copies of interview and questionnaire are available. The transcribed data are consistent with the source documents or the discrepancies are explained with a note in the source document. All entries, corrections, and alterations are made by the investigator or other authorized study personnel.

### Subject Identification and Confidentiality

Subjects are identified by unique study ID numbers, and all paper source documents use this a unique subject number. No personal identifier will be used in any publication or communication used to support this research study. The subject number is used if it becomes necessary to identify data specific to a single subject. Regulatory bodies, such as the IRB, are eligible to review research records related to this study as a part of their responsibility to protect human subjects in clinical research. Personal identifiers are removed from research records.

### Retention of Records

The investigator is responsible for creating and/or maintaining all study documentation required by Title 21 Code of Federal Regulations (21CFR) Parts 50, 54, 56, and 312, ICH E6 section 8, as well as any other documentation defined in the protocol. Federal and local regulations require that the investigator retain a copy of all regulatory documents and records

that support the data for this study for at least 5 years following the date on which the results of the investigation were submitted for scientific publication and/or reported on [clinicaltrials.gov](https://clinicaltrials.gov).

## FINAL STATISTICAL PLAN

### Prevention of Incident Major Depression in Older Adults with Insomnia

#### Statistical Methods and Power Considerations

##### *Sample size*

Meta-analytic data show that insomnia predicts incident depression (odds ratio, OR=2.1; 95% CI). The mean annual incidence of depression is reported at 9.9 in the general population; yet 13.1 in those with insomnia, and 4.0 in those without insomnia. Hence, this study was powered to detect a hazard ratio (HR) of 0.50 between CBT-I vs. SET at 24 months for the primary outcome, with 80% power, two-sided 5%  $\alpha$  level, assuming a small clustering effect (intraclass correlation=0.01), producing a target sample size of 250 (125 per group). Sample size was increased by 10% to consider drop-out. After enrollment and follow-up of 60 participants, annual incidence of depression was 9.6 events; follow-up was extended to 36 months to maintain statistical power at >80%. For the secondary outcome, differences in the rate of insomnia remission between CBT-I and SET in older adults provided an estimated >90% power, two sided 5%  $\alpha$  level.

As noted, DSM diagnostic criteria for insomnia were revised with the duration criterion revised from one month in Diagnostic and Statistical Manual (DSM)–IV to three months in DSM-5. Duration criteria were unspecified in ICSD-2 and specified as 3 months for insomnia disorder in ICSD-3. Eligibility criteria at the onset of the study used insomnia diagnostic criteria as specified DSM-IV and ICSD-2 criteria, and these criteria for inclusion were maintained for the study duration. Hence, it was possible that some enrolled participants did not meet insomnia

diagnostic criteria for DSM-5. To address this possibility, all diagnostic interview data were reviewed for subjects and consensus diagnosis was performed to determine diagnosis using DSM-5 criteria for insomnia disorder, as well as major depressive disorder. Whereas all participants in the enrolled sample met DSM-IV and ICSD-2 criteria for insomnia, some did not meet DSM-5 and ICSD-3 criteria for insomnia disorder. Hence, a post-hoc analysis of the primary outcome was conducted in the subsample who were found to have insomnia disorder at entry as defined by DSM-5.

Exploratory analysis were also performed to assess the survival benefit based on subgroups of interest related to the risk depression incidence as noted in the adjusted model. We estimated treatment effect for each subgroup. Particular subgroups of interest were based on our preliminary findings as noted above including age, sex, medical co-morbidity, use of sleep medications, depression history, use of anti-depressant medications.

For the secondary categorical outcome of remission of insomnia, differences in relative proportions achieved at post-intervention and sustained up to 36 months were tested using mixed regression models adjusting for the above set of covariates.

A predefined secondary analysis examined whether benefit of CBT-I vs. SET was related to treatment effects on remission of insomnia. To provide a robust estimate of insomnia remission and durability of the treatment effect, we categorized participants who showed remission of insomnia at each assessment point and evaluated the extent that such remission is maintained over time (i.e., 36 months). The categorical outcome of interest is sustained remission of insomnia up to the end of follow-up at 36 months. We hypothesized that the benefit of CBT-I would not be achieved if insomnia remission was not achieved and/or if there was a relapse of insomnia or a failure to sustain insomnia remission prior to the depression event. The predefined secondary analysis of the primary outcome, time to incident depression, was performed in which groups were stratified by categorical sustained insomnia remission and a Cox proportional hazard model was used with the SET group with no insomnia remission as

the reference. Exploratory analyses examined the effect of insomnia remission sustained over the follow-up in the total sample using a Cox proportional hazards regression models adjusting for covariates, as reported in the Supplement results.

Missing data were assumed missing at random. Because the CONSORT flow diagram suggested a differential rate of treatment completion and follow-up between the groups, exploratory analyses tested differences between groups in the proportion who discontinued treatment and follow-up. Subsequent analyses then examined possible mechanisms associated with differential discontinuation between the two treatment groups. Differences in sample characteristics by treatment group as a function of discontinuation were tested with repeated measures ANOVA with examination of effects for treatment group, discontinuation status, and the interaction between group and discontinuation status after completion of treatment, 24 months follow-up, and upon entry into the extended 36 month follow-up. Because none of the key demographic or clinical variables were related to discontinuation, further analyses were not performed in the absence of evidence of bias in the results due to differential discontinuation between the groups.

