## **Depression Risk in Older Adults: Significance of Sleep Disturbance**

To maximize efficiency of a prevention intervention in non-depressed older adults, it is also important to identify a profile of modifiable risk factors that can be targeted for intervention. Sleep disturbance or insomnia is one of the most frequent complaints in

depressed patients, which often lingers and its persistence can represent a residual phase of a major mood disorder. Alternatively, emergence of disturbed sleep may serve as a precursor or prodrome of depression, or as a risk factor, for late-life depression occurs. In a meta-analysis of 20 prospective studies, insomnia was a significant predictor of depression onset. In addition, we have found that sleep disturbance, using a questionnaire based screening approach (i.e. PSQI >5) is a predictor of depression incidence among non-depressed elderly community subjects, and that the risk posed by sleep disturbance is greater for depression recurrence than for depression occurrence. Moreover, given that over one-third of those with prior depression history were using antidepressant medications, and such use was not protective in ameliorating the risk of sleep disturbance on depression recurrence, priority evaluation of interventions that specifically target sleep disturbance or insomnia is needed to reduce depressive morbidity in older adults with insomnia; those who have a prior history of depression who may be especially vulnerable to increased rates of depression. There is no prior study that has selectively targeted non-depressed older adults with insomnia to prevent depression incidence, although such a strategy further reduces the NNT to 10, assuming a 50% treatment efficacy. Preliminary data show CBT treatment efficacy at 60% with a NNT of 9.

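### The exploratory subgroup analysis gives an effect per subgroup for six factors but specifies no treatment-by-subgroup interaction, so it does not test whether benefit differs

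*Supplement*

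**What the plan says.** The Final Statistical Plan, under Statistical analysis, introduces the subgroups this way: "Exploratory analysis were also performed to assess the survival benefit based on subgroups of interest". The next sentence is the whole of the method: "We estimated treatment effect for each subgroup". The factors follow: "including age, sex, medical co-morbidity, use of sleep medications, depression history, use of anti-depressant medications". Item 3 of the List of changes in Statistical Plan describes the same approach and adds no test.

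No treatment-by-subgroup term, multiplicity statement or rule for reading differences between strata appears in the final plan. Its only interaction belongs to the discontinuation analysis: "the interaction between group and discontinuation status".

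The size of the trial is set by the overall comparison. Under Sample size: "this study was powered to detect a hazard ratio (HR) of 0.50 between CBT-I vs. SET at 24 months", with 80% power at a two-sided 5% level.

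**The concern.** A list of treatment effects by stratum invites the question of whether CBT-I works better in one stratum than in the other. Stratum estimates alone do not answer it. A trial with about 80% power overall has much less in each half of the sample. Even with the same effect everywhere, one stratum will often reach p<0.05 while the other does not. Gaps between the two point estimates will also be wide by chance.

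At stake is a statement about who benefits that rests on this pattern and not on a test. The exploratory label limits how strongly such a statement may be made. It does not turn within-stratum estimates into a test of difference.

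**Working it through.** The plan gives no figure for the subgroup analyses, so there is none to reproduce. The check asks what stratum-by-stratum results would look like if the HR were the same in everyone.

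**Inputs from the documents**
- Design HR 0.50, two-sided 5%, target 250 (Final Statistical Plan, Sample size).
- 291 participants (Final Protocol, section 12).
- Annual incidence 13.1 with insomnia and 9.6 observed early (Sample size), and 8.6 per 100 person-years in SET (sensitivity analysis paragraph).
- Follow-up of 24 months, extended to 36.
- History of depression in about 30% (Final Protocol, section 5, Eligibility Criteria).

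**Assumptions**
- 13.1 and 9.6 are read as per 100 person-years, since no unit is given. Each rate is applied to SET, although 9.6 is not split by arm.
- Each factor is binary, independent of the others and not prognostic.
- Subgroup shares other than depression history are assumed.

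**Expected events.** With n per arm, SET rate λ, time t and exponential times, E = n × [(1 − e^(−λt)) + (1 − e^(−0.5λt))].

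| N | SET rate | Months | Calculation | Events |
|---|---|---|---|---|
| 250 | 13.1 | 24 | 125 × (0.2305 + 0.1228) | 44 |
| 291 | 13.1 | 24 | 145.5 × (0.2305 + 0.1228) | 51 |
| 291 | 8.6 | 36 | 145.5 × (0.2274 + 0.1210) | 51 |
| 291 | 9.6 | 36 | 145.5 × (0.2502 + 0.1341) | 56 |
| 291 | 13.1 | 36 | 145.5 × (0.3250 + 0.1784) | 73 |

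With 5% loss per year, 291 participants give 49 events (13.1, 24 months), 47 (8.6, 36 months) and 68 (13.1, 36 months). The working range is about 44 to 68.

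**Power within a stratum (Schoenfeld).** Power = Φ(√(E_s/4) × |ln 0.50| − 1.96), where E_s is the events in that stratum.
- 44 events, even split: E_s = 22, Φ(1.63 − 1.96) = 37%.
- 66 events, even split: E_s = 33, Φ(1.99 − 1.96) = 51%.

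**One stratum significant, the other not.** Probability = p1(1 − p2) + p2(1 − p1).
- 44 events, even split: 2 × 0.369 × 0.631 = 0.47.
- 66 events, even split: 2 × 0.512 × 0.488 = 0.50.
- 44 events, 30/70 split: 0.242 × 0.515 + 0.758 × 0.485 = 0.49.

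Treating six factors as independent tests would give 1 − (1 − 0.466)^6 = 98%. That overstates the family figure because all six splits use the same patients, so the family figure needs simulation.

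**Simulation.** Cox models were fitted within each level of six binary factors, with one uniform HR. One set used 800 trials per scenario, with even splits and with shares from 15% to 60%. A second used 3,000 trials per scenario, with three factors at 50%, three at 30% and 5% loss per year; it covered HR 0.50 only. The HR 0.70 and 1.0 columns use 291 participants and the mixed shares.

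| Result under a uniform effect | HR 0.50 | HR 0.70 | HR 1.0 |
|---|---|---|---|
| Discordant significance, per factor | 44-52% | 24-28% | 8-9% |
| Discordant significance, at least one of six | 78-89% | 51-58% | 25-29% |
| Two-fold or larger gap between stratum HRs, at least one of six | 82-89% | 79-83% | 73-76% |
| Interaction p<0.05, per factor | 4-5% | 4-5% | 4-5% |
| Interaction p<0.05, at least one of six | 21-26% | 21-25% | 24% |

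For six independent 5% tests, theory gives 1 − 0.95^6 = 26.5%.

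**What an interaction test can show here.** With 56 events and an even split, the standard error of the log ratio of HRs is √(4/28 + 4/28) = 0.53. The 95% limits are the estimated ratio divided and multiplied by e^(1.96 × 0.53), about 2.9. A true ratio of about 4.5 would be needed for 80% power.

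**The case against.** The strongest reply is that the plan speaks only of estimating effects. It does not say that the sample is split, and a single model with an interaction also yields stratum HRs. It sets no significance test within strata and no rule that discordant p-values show a difference. This stands. A reader might infer that the plan prescribes comparing strata by p-value, or that following it must lead to false claims about who benefits. The documents support neither. The plan is silent on interaction; it does not exclude it. The discordance rates describe a misreading that the plan leaves open.

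Several further limits also stand:
- A high chance of discordance is not a general property of the design. It holds near HR 0.50 and drops to about one trial in four at HR 1.0.
- Setting the six-factor discordance figure beside the 4-5% per-factor interaction rate would compare unlike quantities. The like-for-like family figure is 21-26%.
- The background finding that "the risk posed by sleep disturbance is greater for depression recurrence than for depression occurrence" (Final Protocol, section 2) concerns prognosis in a cohort. It is not evidence that CBT-I works differently by depression history.
- Targeting, in the Design Overview, means finding older adults with insomnia by questionnaire. It does not mean selecting among them by these six factors.
- No primary or secondary hypothesis rests on the subgroups.

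What does not stand is that the omission is only wording. Without an interaction, no specified analysis addresses a difference between subgroups. Restricting attention to point estimates does not help either: two-fold gaps arise by chance in 73-89% of trials for at least one factor.

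**Conclusion.** The point holds as an omission: effects are reported by subgroup for six factors, and no test of whether they differ is specified. If strata were compared by significance under a uniform HR of 0.50, at least one apparent difference would be expected in about four trials in five or more. Interaction tests reduce that to about one in four. They do not remove the chance gaps between point estimates.

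The sizes rest on 44 to 68 events, binary and non-prognostic factors, and assumed shares apart from depression history. Even and uneven shares gave similar results. The documents do not say that age or co-morbidity is dichotomised. A reader might infer that the trial's main conclusion is weakened. It is not: the primary Cox comparison does not depend on these analyses. The appropriate label is a cheap improvement.

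**What to change.** For each listed factor, fit one Cox model with treatment, the factor and treatment-by-factor. Report the interaction estimate (the ratio of HRs) with its 95% CI and p-value, and take the stratum HRs from that model. State that a difference between subgroups is suggested only on the interaction, and that the six tests are exploratory, not adjusted for multiplicity and low in power.

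The cost is a few sentences in the plan and one extra term per model. No new data are needed. The drawback is that most interaction results will be inconclusive, which is what this number of events can support.

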## **List of changes in Statistical Plan**

1. For the primary analysis, an additional exploratory analysis adjusted for severity of depressive symptoms and use of antidepressant and sedative hypnotic medications, as well as the predefined set of covariates including sex, education, income, co-morbidity, and previous history of depression. These exploratory analyses were performed using this set of covariates, because each has been reported to be associated with risk of incident depression
2. Because DSM diagnostic criteria for insomnia were revised with the duration criterion revised from one month in Diagnostic and Statistical Manual (DSM)–IV to three months in DSM-5, and eligibility criteria at the onset of the study used insomnia diagnostic criteria as specified DSM-IV and ICSD-2 criteria, a post-hoc analysis of the primary outcome was conducted in the subsample who were found to have insomnia disorder at entry as defined by DSM-5.
3. Exploratory analysis were performed to assess the survival benefit based on subgroups of interest related to the risk depression incidence as noted in the adjusted model. We estimated treatment effect for each subgroup. Particular subgroups of interest are based on our preliminary findings as noted above including medical co-morbidity, use of sleep medications, depression history, use of anti-depressant medications.
4. We performed an exploratory analysis to examine whether sustained remission of insomnia was associated with survival benefit. This secondary analysis was in addition to the predefined secondary analysis of the primary outcome, time to incident depression, in which we stratified treatment groups by categorical sustained insomnia remission and use a Cox proportional hazard model with the SET group with no insomnia remission as the reference. These additional exploratory analyses examined the effect of insomnia remission sustained over the follow-up in the total sample, as opposed to stratified treatment groups, using a Cox proportional hazards regression models adjusting for covariates.

5. Exploratory analyses related to the inflammatory outcomes were not performed, as this reported finding from the primary outcome analysis.
6. Missing data were assumed missing at random
7. Exploratory analyses examined the differential rate of treatment completion and follow-up between the groups, and whether there were differences in sample characteristics by treatment group as a function of discontinuation repeated measures ANOVA with examination of effects for treatment group, discontinuation status, and the interaction between group and discontinuation status after completion of treatment, 24 months follow-up, and upon entry into the extended 36 month follow-up.
8. Sensitivity analyses were performed to examine differences between observed and complete data sets. These analyses utilized multiple ( $i=100$ ) imputed datasets to assess scenarios for complete data. For the primary outcome, unobserved depression incidence (i.e. for those who withdrew from the study prior to the 3 year follow-up) was modeled using a Pareto distribution based on the observed and range of assumed incidence of depression in SET (8.6 events per 100 person years, 95% CI, 3.8 – 13.3 events per 100 per years). An adjusted Cox proportional hazards regression model examined time to incident depression for complete data sets. For secondary analyses of insomnia remission, complete datasets were generated using an iterative Markov chain Monte Carlo (MCMC) method.

